## Overview of ACT-HF trial design

2

ACT-HF is a multi-center cluster-randomized behavioral-intervention trial that will recruit and randomize clinicians to receive access to the intervention software (Anumana's Guideline Navigator) or provide usual care.

Clinicians (≤250) will be recruited from 2 health systems to participate in the ACT-HF Study. Participants will be clustered at the care team level within each site. The trial will evaluate the clinical care provided during >2148 eligible clinical encounters and 90 days following the index encounter. Clinicians will be consented and randomized into intervention or care as usual; patients are not recruited for this study (Fig. 1).

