## Study intervention software

4

Anumana has developed an innovative AI-enabled clinical decision support system - Guideline Navigator which is a multi-module software solution with a user interface. Guideline Navigator connects with the electronic health record (EHR) through an application program interface (API) to (1) rapidly analyze patient clinical data (2) harmonize structured data, (3) curate unstructured clinical notes with natural language processing (NLP), (4) interpret patient data using a Bidirectional Encoder Representations from Transformers (BERT) model to complete an automated chart review, (5) evaluate alignment to guideline directed medical therapy (GDMT) for heart failure with reduced ejection fraction (HFrEF) using a machine learning model trained to identify eligible patients with potential gaps in care, (6) identify relevant indications and contraindications, (7) summarize potential GDMT gaps-to-care with a point-of-care user interface for clinicians to review, and (8) trigger a point-of-care alert to notify clinicians of potential opportunities to optimize clinical care for patients with HFrEF (Anumana, data on file).

Guideline Navigator software is integrated within each participating health system's EHR and access is restricted to the participating clinicians. For the purposes of the ACT-HF study, Guideline Navigator will process the EHR data for eligible clinical encounters on the night prior to an appointment; clinicians may also reprocess the results at point-of-care to incorporate any updated prescription information that was made during patient check-in. A wrong recommendation will not be considered an adverse event, unless there is an event as a consequence of such. All others will be considered errors, but not adverse events. Clinicians randomized to the intervention group receive an alert (Fig. 2) for any eligible encounter with actionable results from the Guideline Navigator software; there is no alert for ineligible clinical encounters or for clinicians randomized to the standard of care group. The clinician may receive multiple alerts for a patient for a return patient who remains non-compliant with GDMT during the study period.

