• Change in patient NYHA Class from baseline through observational period • % of patients taking optimal GDMT-HF therapy based on software-identified indications and lack of contraindications • Time to start of new GDMT-HF medication class • Dosage of GDMT-HF-recommended quad therapy HFrEF medications reached • % of patients for whom at least one GDMT-HT medication was prescribed.	• User engagement with the software, including session counts, session duration, and report button click counts. • Percent of notification prompts that are accepted or dismissed, at the clinician level. • Clinician experience with software (survey-based) o Cognitive behavioral, and contextual factors related to clinician satisfaction, acceptance, and use of the software o Reasons for rejecting, modifying, or ignoring recommendation o Barriers and facilitators to use	• Changes in BNP or NT-pro-BNP, blood potassium, blood creatinine, and estimated glomerular filtration rate • Hospitalizations o Heart Failure o All-cause • Mortality o Heart Failure o All-cause • Indicators of resource utilization o Ordering of echocardiogram, time from index encounter, and echocardiogram results o Outpatient appointments o Specialist visits o Hospital days o Emergency room visits o 30 day readmissions following a heart failure hospitalization

ACT-HF Study - Safety endpoints
• Incidences and event rates of study-related adverse events (AE), compared to control arm • Incidences and event rates of study-related Severe Adverse Events (SAE), compared to control arm

Adverse events (AE) and severe adverse events (SAE) will also be reported throughout the duration of the study, as applicable. For the purposes of the ACT-HF study, adverse events include death, side effects or allergies to a medication that was started due to a failure of the software to identify prior side effects or allergies and the clinician fails to check for prior side effects or allergies, or other reportable events. ACT-HF is a minimal risk study and AE/SAEs are not anticipated. If any AE/SAE occurs during the study, clinician participants are asked to notify the Site PI or designee to report the event within 24 h of knowledge of the event.

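### The safety endpoints compare the arms, yet the only drug-harm event named in the AE definition can arise in the intervention arm alone

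*Protocol article*

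**What the plan says.** The safety block of Table 1 (ACT-HF study endpoints) has two lines: "Incidences and event rates of study-related adverse events (AE), compared to control arm" and "Incidences and event rates of study-related Severe Adverse Events (SAE), compared to control arm". Both ask for a contrast with usual care.

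The paragraph after the table says what counts: "adverse events include death, side effects or allergies to a medication that was started due to a failure of the software to identify prior side" reactions. It adds a second condition and a residual category: "the clinician fails to check for prior side effects or allergies, or other reportable events". The section on the study intervention software adds a further rule: "A wrong recommendation will not be considered an adverse event, unless there is an event as a consequence of such".

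The trial overview describes the randomised contrast: the trial will "randomize clinicians to receive access to the intervention software (Anumana's Guideline Navigator) or provide usual care". The software section confirms what this means for control: "there is no alert for ineligible clinical encounters or for clinicians randomized to the standard of care group".

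**The concern.** A between-arm safety comparison needs an event that can occur, and be counted, in both arms. The one drug-harm event spelled out here is defined by the intervention itself, because it requires a software failure. Usual care has no software that could fail, so for this event the comparator is empty before any data are collected. Complete or blinded reporting would not change that.

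The definition is also narrow where it matters most. The intervention is meant to increase prescribing, so the most direct route to patient harm is an ordinary side effect of a newly started drug that was properly recommended. That event is not named as an AE in either arm.

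At stake is whether the stated safety comparison can answer its own question for drug harm. A result of no events in either arm could be taken as reassurance. A few intervention events against a forced zero could be taken as excess harm. Neither would estimate the difference in drug harm between software-supported care and usual care.

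**Working it through.** The article gives no safety rate, margin, test or power, so there is no figure to reproduce. The check is mainly one of logic.

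**Step 1. Which named events can occur in each arm?**

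| Item counted as an AE | Needs the software? | Possible under control care? |
|---|---|---|
| Death | No condition stated | Yes, unless *study-related* excludes it |
| Reaction to a drug begun because the software missed an earlier reaction and the clinician did not check | Yes | No |
| Event that follows a wrong recommendation (software section) | Yes | No |
| Other reportable events | Not defined | Depends on the definition |
| Side effect of a new drug that was correctly recommended, or begun under usual care | No | Would occur in both arms, but is not named |

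**Step 2. The drug-harm component.** Write p_I and p_C for the event probabilities under intervention and control. The definition requires a software failure and control has no software, so p_C = 0. Then p_I − p_C = p_I ≥ 0, and p_I / p_C is undefined. The comparison reduces to the intervention count and carries no information about drug harm under usual care. If a control patient were also treated by an intervention clinician and had such an event, that would be contamination, not a usual-care rate.

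**Step 3. The whole endpoint.** Two readings of *study-related* are open.

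- *Caused by the software.* The software-dependent rows are zero in control, and control deaths drop out too. The comparator is then empty.
- *Any listed event during the study.* Deaths count in both arms. To see how far from empty this is, assume 1:1 allocation (the article gives no ratio), one index encounter per patient and no clustering. That gives 2148 / 2 = 1074 per arm. The article states no 90-day mortality, so a range is assumed:

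| Assumed 90-day mortality | Expected control deaths (1074 × m) | Chance of none, (1 − m)^1074 |
|---|---|---|
| 1% | 10.7 | 0.00002 |
| 2% | 21.5 | 4 × 10⁻¹⁰ |
| 4% | 43.0 | 9 × 10⁻²⁰ |

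On this reading the control rate is clearly not zero, but the endpoint mixes deaths from both arms with drug reactions that can come from one arm only.

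**Step 4. What the named drug-harm event leaves out.** For scale only, suppose the alert leads 10 percentage points more patients to start a drug, and 2% to 10% of them have a side effect. Both figures are assumptions. Extra starts are 1074 × 0.10 = 107.4. Extra side effects are 107.4 × 0.02 = 2.1 to 107.4 × 0.10 = 10.7. Those that follow a correct recommendation are not named as AEs, and could enter only through the undefined residual category.

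The conclusion rests on Steps 1 and 2. The figures in Steps 3 and 4 are illustrations.

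**The case against.** The strongest reply is that the control rate is not zero for the endpoint as a whole. A reader might infer from the drug-reaction wording that it is. The article does not support that: death is listed with no software condition, other reportable events are left open, and the list is introduced as non-exhaustive. An empty control arm follows only if *study-related* means software-related, which the article never says. This part of the reply stands.

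A second reply is that Table 1 already lists exploratory outcomes that do not depend on the software: heart-failure and all-cause mortality and hospitalization, emergency visits, potassium, creatinine and eGFR. They can show some harm from added prescribing, so it would be wrong to say that the trial has no fair between-arm information on harm. This also stands. But they are not the safety endpoints, and they do not capture allergies or most drug side effects.

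Third, a reader might infer that a drug side effect counts only when the software missed an earlier reaction. That is too strong, because the software section also counts any event that follows a wrong recommendation. This route needs software exposure as well, so it does not repair the comparison.

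Fourth, the meaning of *study-related* and the full list of reportable events may sit in the full protocol, and their absence from an article is no fault in itself. That is fair. The defect lies in what the article does state: a comparison with control, and a drug-harm definition that control care cannot meet. An analysis plan could not make that component estimable without changing the definition.

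**Conclusion.** The concern holds for the drug-harm component. As defined, its control rate is zero by construction, its difference can only be zero or unfavourable to the software, and its ratio is undefined. For the full AE and SAE endpoints, the control rate turns on an undefined term and cannot be called zero by definition. Side effects of correctly recommended new drugs are not named in either arm, and the exploratory outcomes fill that gap only in part.

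This conclusion rests on the wording of the AE definition and on the absence of alerts in the control arm. It needs no assumption about event rates, allocation or clustering. The primary endpoint is unaffected. The change should be made, because the stated safety comparison otherwise cannot answer its own question for drug harm.

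**What to change.** 1. Report software-attributed events (a missed earlier reaction, or an event that follows a wrong recommendation) descriptively for the intervention arm only, with no arm comparison.
2. Replace the two safety lines in Table 1 with a comparison that applies equally to both arms: documented side effects or allergies to guideline-directed drugs started within 90 days of the index encounter, whether or not the software was involved, abstracted from the EHR by the same rules in both arms.
3. Present alongside it the all-cause mortality, hospitalization and laboratory outcomes already listed as exploratory.
4. Align the AE definition with these lines, and state what *study-related* means wherever the term is kept.

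The cost is small. The study data collection section already has EHR data evaluated at the index encounter and 90 days later in both groups, and the endpoints section already has a research coordinator abstracting clinical outcomes. The change adds rewording and one abstraction item, which may take more effort where side effects are recorded only in free-text notes. Stated AE rates will rise in both arms, against the article's expectation that none will occur. The software prompts intervention clinicians to look at contraindications, so side effects may be documented more fully in that arm. Identical abstraction does not remove this, and the interpretation should say so.

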## Discussion

7

The 2022 Clinical Practice Guidelines for Heart Failure Management provide the strongest class of recommendation for optimizing GDMT quad-therapy for patients with HFrEF, based on endpoint data from several randomized clinical trials [2]. The 2022 HF Guideline added the SGLT2i class of medications to the previous GDMT which recommended three classes of medications (triple-therapy) based on evidence available at the time: RAASi, Beta Blockers, and MRA [10]. In a real-world study of GDMT triple-therapy adherence, incomplete adherence to GDMT triple-therapy was associated with 29 % excess mortality risk in two year follow up [11].

In addition to the classes of medication in GDMT, timely achievement of the target dose of the classes of medications is an important factor in outcomes for patients with HFrEF. A multinational study of Utilization of Dapagliflozin and Other Guideline Directed Medical Therapy in Heart Failure Patients: (EVOLUTION-HF) reported that the mean time from HF hospitalization to GDMT initiation were longer for novel GDMT classes compared to other GDMT classes in Japan, Sweden, and the United States [12]. Further, an analysis of nearly 5000 patients without contraindications in the Change the Management of Patients with Heart Failure (CHAMP-HF) registry demonstrated reduced mortality with target dosing of RAASi and Beta Blocker Medications [13]. These data highlight the importance of managing the classes, timing, and quantities of GDMT medications.

Despite substantial evidence supporting GDMT for HFrEF, medical management of HFrEF patients falls short and adherence remains low. An analysis of data from the PINNACLE (Practice Innovation and Clinical Excellence) Registry of ambulatory care in heart failure reported that 60.7–71.4 % of ambulatory patients with HFrEF received Beta Blockers and RAASI medications from 2013 to 2017 [14]. In the CHAMP-HF Registry, only 1 % of patients were receiving the standard of care GDMT triple-therapy at the time of the study [15]. Among HF patient groups, disparities in care also exist among patients of color, despite high HF prevalence [16,17] and among females compared to males [18].

Several recent studies have evaluated novel methods and tools to improve medical management and medication adherence in HFrEF through patient/provider interventions, including: PRagmatic trial Of Messaging to Providers about Treatment of Heart Failure (PROMPT-HF) [19], Building Electronic Tools to Enhance and Reinforce Cardiovascular Recommendations for Heart Failure (BETTER CARE-HF) [20], Safety, tolerability and efficacy of up-titration of guideline-directed medical therapies for acute heart failure (STRONG-HF) [21], and Safety And Efficacy Of Virtual Care Team Guided Therapeutic Optimization During Hospitalization In Patients With HFrEF (IMPLEMENT-HF) [22]. Specifically, PROMPT-HF reported a > 40 % greater GDMT prescribing among clinicians who received a point-of-care EHR-based alert, compared to usual care in a single ambulatory care center [19]. Similarly, BETTER CARE-HF compared the effectiveness of an automated alert or message to usual care in MRA prescribing patterns in an outpatient cardiology practice; and reported that the automated alert was more effective than both message and usual care [20]. Investigators in the STRONG-HF study reported that rapid uptitration of GDMT and closely following hospitalized HF patients post-discharge was effective at reducing 180-day all-cause mortality and heart failure readmission rates compared to usual care across health systems in 14 countries [21]. Lastly, IMPLEMENT-HF demonstrated that a virtual care-team approach which reviewed charts of patients hospitalized with HFrEF and provided recommendations for GDMT optimization increased the use of β-blockers, ARNI, MRA, and triple-therapy compared to usual care [22].

The ACT-HF Study and the Guideline Navigator software were designed with the learnings from these studies as guides to drive improvement in GDMT adherence with novel methods, by leveraging a novel end-to-end software platform, Anumana's Guideline Navigator, and a point-of-care alert to notify clinician participants of the potential deviation from GDMT. ACT-HF is a multi-center study to evaluate the clinical effectiveness of Guideline Navigator, which automates chart review of both structured and unstructured data in the EHR to synthesize and present the key data in medication management: diagnoses, current medications, indications, and contraindications. ACT-HF will also evaluate study endpoints and subgroup analyses to further refine the Guideline Navigator software for improved clinical utility, workflow integration, and patient outcomes. We project that the observational period will complete in May 2025 with 90-day data readout and primary analyses available in late 2025. Analysis of endpoints and subgroup analyses may be presented later in 2026. Subgroup analyses may include evaluation of outcomes by site-level, clinician-level, or patient-level characteristics, examples may include site geography, participant professional characteristics, or patient medical history.

There are limitations to the ACT-HF study that must be considered. First, the study success depends on the successful integration of the study software within each study site's secured EHR system. Because of the sensitive nature of patient EHR data, this process requires several reviews and approvals before the software environment can be made available for testing. Also, study outcomes depend on user engagement with the software. Intervention group clinicians will be trained on the Guideline Navigator software at consenting but are not required to use the study software for clinical decision making. To address this potential bias, the study will include a subgroup analysis comparing study outcomes among Low Adopters and High Adopters of the software. Additionally, the ACT-HF study is designed to evaluate the feasibility of deploying an EHR-integrated software, Guideline Navigator, to identify and remediate non-compliance to GDMT; the primary endpoints do not explore cost considerations, implications, and barriers of additional prescribing. Before this or similar tools are deployed in broader clinical setting beyond this randomized study, a thorough evaluation of stakeholder costs is warranted to ensure that the software does not exacerbate health disparities.

In this first-of-its-kind, multicenter analysis, the ACT-HF Study will evaluate the impact of a novel CDS software to impact optimal GDMT for HFrEF, including clinician experience and engagement with the software. ACT-HF will also evaluate clinician acceptance of the Clinical Practice Guidelines, as well as self-reported acceptance of the CDS. The goal of the intervention is to (1) increase GDMT adherence, (2) reduce health disparities by helping to identify opportunities at point-of-care to identify patients or patient groups who may be at risk of suboptimal GDMT through an automatic system that will not be influenced by socioeconomic status, gender, race or ethnicity, and (3) reduce cognitive burden in busy clinical settings across geographically diverse clinical settings.

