## Study data collection

5

Study data will be collected from participant surveys, study software metrics, and EHR data as a read-out for clinician decision-making. Surveys were designed by experts in computer-human interaction and healthcare delivery research to quantitatively assess knowledge, readiness, usability, and acceptance of the software with questions designed to evaluate decision-making behavior, clinician sentiment towards technology-based clinical decision support solutions, and clinical inertia.

Clinician participants may discuss results with patients; however patients will not have direct contact with the study team or direct access to the ACT-HF Study software or software output. Guideline Navigator will only provide recommendations for HFrEF patients who are not currently prescribed optimal GDMT.

EHR data will automatically be collected in a privacy-preserving manner and all data will be deidentified and analyzed in the aggregate, to avoid accidental disclosure of protected health information (PHI). EHR data will be evaluated at the Index Encounter and 90-days following the Index Encounter to evaluate whether there were any changes in treatment patterns in both control and intervention groups. Pre-study surveys will be conducted to evaluate clinicians' knowledge of GDMT and their readiness to adopt the new technology. Post-study surveys will be conducted to further examine usability and acceptance of the CDS software.

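### The Low versus High Adopter comparison is offered as the answer to bias from voluntary use, but it is a non-randomised contrast within one arm and cannot serve that purpose

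*Protocol article*

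**What the plan says.** The limitations paragraph of the Discussion makes three linked statements. Engagement drives results: "Also, study outcomes depend on user engagement with the software". Intervention clinicians are trained but "are not required to use the study software for clinical decision making". The remedy follows: "To address this potential bias, the study will include a subgroup analysis comparing study outcomes among Low Adopters and High Adopters of the software". This is a commitment with a stated purpose, whereas the other subgroup analyses in the same section are described only as possible.

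Elsewhere the article fixes what is randomised. The trial will "recruit and randomize clinicians to receive access to the intervention software (Anumana's Guideline Navigator) or provide usual care" (Overview of ACT-HF trial design). On the control side, "there is no alert for ineligible clinical encounters or for clinicians randomized to the standard of care group" (Study intervention software). Table 1 lists the engagement measures: "User engagement with the software, including session counts, session duration, and report button click counts", together with the percentage of prompts accepted or dismissed by each clinician. The one relevant baseline measure is in Study data collection: "Pre-study surveys will be conducted to evaluate clinicians' knowledge of GDMT and their readiness to adopt the new technology". The article does not connect that survey to the adopter grouping, and it does not define Low or High Adopter.

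**The concern.** The problem named is real: if many intervention clinicians ignore the tool, the contrast between arms is diluted. Splitting the intervention arm by use does not repair this. Use is decided after randomisation, by the clinician, and control clinicians have nothing to adopt. A difference between High and Low Adopters therefore mixes any effect of the software with the reasons why some clinicians use it more.

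Three such reasons follow from the article's own design:

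- **Prescribing tendency.** Clinicians keen to optimise therapy may open the tool more. They may equally use it less, because alerts arise only for patients not on optimal therapy.
- **Caseload.** Session and click counts grow with the number of eligible patients seen.
- **Repeat alerts.** A returning patient who is still not on guideline therapy can trigger further alerts, so the opportunity to use the tool depends partly on the outcome itself.

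At stake is what may be concluded. A reader told that the analysis addresses bias could take an observational contrast as randomised evidence about what the software does when it is used.

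**Working it through.** **1. Logic, from the article.** Access is randomised and level of use is not. The engagement measures in Table 1 all accrue after allocation and only under the intervention. The Low/High contrast therefore has no randomised comparator.

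**2. Is there a figure to reproduce?** No. The article gives at most 250 clinicians and more than 2148 encounters, without alpha, power, SD or ICC. The point does not depend on these figures; what follows only shows how large the distortion could be.

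**3. Inputs for the illustration.**
- From the article: 2148/250 = 8.6 patients per clinician, taken as 9; 250/2 = 125 intervention clinicians.
- Assumed: true software effect zero; outcome SD 1; adopters split at the median; clinician ICC 0.02 to 0.10; correlation r between adoption and the clinician's own prescribing tendency 0 to 0.5; clinicians independent. The article clusters by care team, which is not modelled here.

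**4. Expected spurious difference.** High minus Low = 2 × √(2/π) × r × √ICC, in SD units. For r = 0.3 and ICC = 0.05: 1.596 × 0.3 × 0.2236 = 0.107.

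**5. Detectable effect between arms, for scale** (two-sided 5%, 80% power, 1074 per arm, assumed). Without clustering: (1.96 + 0.842) × √(2/1074) = 0.121 SD. With clustering, multiply by √[1 + (8.592 − 1) × ICC]. This gives 0.130 at ICC 0.02 (√1.152 = 1.073), 0.142 at 0.05 and 0.160 at 0.10. Using 9 patients per clinician gives about 0.143 and 0.162 for the last two.

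**6. Results** (formula for the difference; 3000 simulated trials per row for the rejection rate).

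| ICC | r | Spurious High − Low (SD) | Share with p < 0.05 | Detectable between arms (SD) |
|---|---|---|---|---|
| 0.02 | 0 | 0 | 5% | 0.130 |
| 0.02 | 0.3 | 0.068 | 19% | 0.130 |
| 0.02 | 0.5 | 0.113 | 43% | 0.130 |
| 0.05 | 0 | 0 | 5% | 0.142 |
| 0.05 | 0.3 | 0.107 | 34% | 0.142 |
| 0.05 | 0.5 | 0.178 | 73% | 0.142 |
| 0.10 | 0 | 0 | 5% | 0.160 |
| 0.10 | 0.3 | 0.151 | 48% | 0.160 |
| 0.10 | 0.5 | 0.252 | 90% | 0.160 |

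**7. Hand check of one row** (ICC 0.05, r = 0.3). Variance of a clinician mean = 0.05 + 0.95/9 = 0.156. SE of the difference = √0.156 × √(2/62.5) = 0.071. Then z = 0.107/0.071 ≈ 1.5, and rejection is about 33%, in line with the simulated 34%.

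**8. Other contrasts.** In the rows with r above zero, High Adopters against all controls is biased by about half as much (0.03 to 0.13 SD). The comparison of arms as randomised stays within 0.004 SD of zero in every row.

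A negative r reverses the sign of the spurious difference and leaves its size unchanged.

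**The case against.** The strongest case against has four parts.

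*The analysis is secondary.* The primary endpoint is already compared with care as usual, by arm. Subgroup work is said elsewhere in the Discussion to serve refinement of the software, and describing outcomes by uptake is ordinary in implementation research. This stands and limits the reach of the point. A reader might infer that the trial's main result is compromised; the article does not support that.

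*Adopter is undefined.* The full protocol or analysis plan may supply a definition, a model or baseline adjustment. The share of prompts accepted, also in Table 1, does not rise mechanically with caseload. That weakens the caseload argument for that measure. The measure is still recorded after allocation and in one arm only. A definition based on baseline readiness would escape the criticism, but the sentence speaks of adopters of the software, directly after voluntary use. No unseen definition based on actual use can make the published purpose correct.

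*The direction is unknown.* A reader might infer that High Adopters would look better even if the software did nothing. The documents do not show this. Clinicians who already optimise therapy may generate fewer alerts, and repeat alerts go to patients whose therapy has not improved.

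*The size is assumed.* No ICC or correlation is given. A reader might also infer that the spurious difference is as large as the effect the trial could detect. Once clustering is applied to both figures, this is true in only two of the six scenarios with a non-zero correlation (r = 0.5 with ICC 0.05 or 0.10). At r = 0.3 the spurious difference is smaller in every row.

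**Conclusion.** The concern holds as a fault in the stated purpose of one analysis. A Low versus High Adopter comparison is non-randomised, and it cannot address bias from voluntary use or estimate the effect of use. This conclusion follows from the design and needs no numerical assumption beyond reading adoption as actual use, which is what the text indicates.

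Its size cannot be established from the article. Under the assumptions listed, the distortion ranges from none to about 0.25 SD and the false-positive rate from about 5% to 90%, and the sign could go either way. The analysis is acceptable as description. The correction is worth making because it changes what may be concluded from the adopter results, although the primary analysis needs no change.

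**What to change.** 1. Delete the opening phrase that presents the adopter comparison as a remedy for bias. Report Low and High Adopter outcomes descriptively, labelled as non-randomised, with the definition of adoption stated.
2. State that the comparison of arms as randomised is the only answer on effectiveness.
3. For effect modification, fit an arm-by-baseline-readiness interaction, using the pre-study survey of "their readiness to adopt the new technology". This requires the survey to be completed in both arms before the intervention starts, which the article does not say explicitly. It asks a different question from the effect of use.
4. If an effect in users is wanted, add a complier-average analysis as a sensitivity analysis only, with arm as the instrument and cluster-robust errors. Training and alerts can change prescribing without any session or click, so use must be defined to include exposure to the alert, and the exclusion restriction must be stated. With that definition most intervention clinicians may count as users, and the estimate may then differ little from the comparison by arm.

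The cost is a change of wording and one extra model, or two if the complier-average analysis is added. The user-level claim also becomes weaker.
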